## Introduction

### Background

Cardiac surgery is a common life-saving procedure [1] that can lead to several complications during recovery. One of them is persistent postoperative pain (ie, pain developing after surgery and lasting at least 3 months with other causes of pain excluded [2]), and its incidence seems to have increased [3]. Estimates suggest that up to 37% of patients undergoing cardiac surgery have persistent pain and will potentially develop chronic postsurgical pain (CPSP; ie, pain lasting for more than 3 months following surgery), with 50% of them reporting moderate to severe postoperative pain [3] that compromises their recovery and daily functioning [3-6]. Furthermore, 10% of the patients will develop new prolonged opioid use (ie, opioid use for more than 3 months) [7], which portends addiction and overdose death [8]. Both chronic pain and chronic opioid use can exacerbate heart disease [9-14]. Compounding this human cost, CPSP is expensive, incurring annual direct and indirect costs of US $41,000 per patient in the United States [15].

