### Settings and Participants

To be able to provide precise estimates of mean and variance that will aid in the planning of a larger and sufficiently powered efficacy trial, a reasonable rule of thumb for continuous variables (eg, pain intensity) is a sample size of 12 per group [78]. Based on previous experience with this population and intervention, we could expect an attrition rate of 20%. However, an attrition rate of 30% could be anticipated in the long term at the 6-month follow-up [43]. Hence, we will recruit 32 participants—16 (50%) per group. Patients will be selected according to the following criteria: (1) age ≥18 years, (2) first-time elective coronary artery bypass grafting and valve replacement via a median sternotomy, (3) worst pain in the past week score ≥4/10 [79], (4) ability to understand and complete questionnaires in English, and (5) ability to use an electronic device such as a smartphone, computer, or tablet. Patients will not be eligible for the study if they (1) had undergone a previous thoracotomy or mastectomy and (2) were unable to consent because of physical or cognitive incapacity.

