### Data Collection

As mentioned, measures will be taken via a telephone interview using Qualtrics for data entry. Given the pilot nature of this study and the timeline of the CPSP trajectory [85], all measures, except for acceptability and feasibility of the intervention, will be taken before the intervention (T0), after the intervention (T1), 3 months after surgery (T2), and 6 months after surgery (T3) for both groups [85]. Usual sociodemographic variables (ie, age, sex, civil status, living conditions, education level, and employment status) will be assessed. Relevant medico-surgical information during hospitalization will be collected: type of surgery, presence of postoperative complications, length of hospital stay, and current involvement in a rehabilitation program. The presence of chronic pain before surgery will also be documented. Considering established relations between pain, anxiety, and depression [86-88], measures of anxiety and depression will be taken with the Patient Health Questionnaire-4 for depression and anxiety [89] at all time points. The validity and reliability of the Patient Health Questionnaire-4 has been well established [89-91].

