Regarding the preliminary effects of the intervention, the protocol will favor an intention-to-treat approach for the analysis of results, thus involving all patients who were randomly assigned. Participants’ flow will be reported according to the Consolidated Standards of Reporting Trials guidelines for psychological interventions [109]. The statistical analysis will be mostly descriptive (mean and SD for continuous outcomes and frequency and proportion for categorical outcomes) with 95% CIs when appropriate. Pain intensity, pain interference, opioid use, mindfulness, pain acceptance, pain-related catastrophic thoughts, and depression or anxiety scores will be summarized using descriptive statistics presented per group at each time point. Furthermore, treatment effects will be estimated and presented with 95% CIs at each time point. Between-group differences will be assessed by fitting linear mixed models for each outcome: pain intensity, pain interference, opioid use, mindfulness, pain acceptance, pain-related catastrophic thoughts, and anxiety or depression. Outcome variables will be regressed on the intervention group (EG vs ACG) and time (preintervention, postintervention, and 3 and 6 months after surgery) after covarying baseline values to perform statistical matching on prerandomized values, thus ensuring that comparisons by treatment group are independent of baseline differences [110]. Of primary interest is the impact of the intervention on the prevalence and severity of CPSP (ie, pain intensity, pain interference, and opioid use) at 3 and 6 months. However, these analyses will be undertaken primarily for illustrative purposes, as the study is not powered to show statistical significance. An α level of significance of .05 will be used for all analyses.

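### CPSP prevalence is of primary interest, but the listed analyses contain no CPSP case variable, and the measures as described do not separate surgical from long-standing pain

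*Protocol article*

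**What the plan says.** **Target.** The Statistical Analysis section of the protocol article states: "Of primary interest is the impact of the intervention on the prevalence and severity of CPSP (ie, pain intensity, pain interference, and opioid use"), with 3 and 6 months after surgery as the time points. It adds that these analyses are mainly illustrative and that the study is not powered.

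**Analysis.** The same section states: "Between-group differences will be assessed by fitting linear mixed models for each outcome: pain intensity, pain interference, opioid use, mindfulness, pain acceptance", followed by catastrophic thoughts and anxiety or depression. The outcomes to be summarised per group at each visit are the same set. Neither list contains CPSP. A general line provides for "frequency and proportion for categorical outcomes".

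**Definitions.** The Background defines persistent postoperative pain as "pain developing after surgery and lasting at least 3 months with other causes of pain excluded". It glosses chronic postsurgical pain more loosely: "CPSP; ie, pain lasting for more than 3 months following surgery".

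**Who enters and what is asked.** Under Settings and Participants, the pain criterion is "worst pain in the past week score ≥4/10". The only exclusion bearing on earlier pain is for patients who "had undergone a previous thoracotomy or mastectomy". The Pain section describes four 0-10 ratings that differ by average, worst or present pain, by recall period, and by movement or rest. Under Data Collection: "The presence of chronic pain before surgery will also be documented". No use of that variable is stated.

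**The concern.** There are two linked problems.

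First, the stated target and the stated analysis do not match. An effect on prevalence is a contrast between two proportions of cases. A linear mixed model of a 0-10 rating or an interference total gives a difference in mean scores. That speaks to severity, but it does not say how many participants have CPSP in each arm. If no case definition is fixed in advance, any proportion reported later would rest on a cut-off that could be chosen after the data are seen.

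Second, the intervention is presented as preventing pain from becoming chronic after surgery. A participant with long-standing back or joint pain can meet the entry criterion as described and can still give a high rating at 3 and 6 months. Pain that predates the operation cannot be prevented from developing, so counting it as CPSP would weaken any preventive contrast.

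**Working it through.** **1. Target set against analysis**

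| Element | What the article gives | Does it yield prevalence? |
|---|---|---|
| Primary interest | Prevalence and severity of CPSP at 3 and 6 months | Named as the target |
| Bracketed gloss | Pain intensity, pain interference, opioid use | No; none is CPSP case status |
| Between-group models | Linear mixed models on the listed outcomes | No; CPSP is not in the list |
| Per-group summaries | The same outcomes at each visit | No; CPSP is not in the list |
| General line on categorical outcomes | Frequency and proportion | Only if a case variable is defined; none is named |

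The severity half of the target is covered. The prevalence half is not.

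**2. Separation of surgical from other pain**

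The entry criterion has a threshold and a recall period. The pain items have a recall period and a movement or rest condition. Neither, as described, has a site, an onset or an attribution. The prior-surgery exclusion and the restriction to first-time cardiac surgery remove some earlier chest-wall pain, but not back or joint pain. Chronic pain before surgery is recorded and then not mentioned again.

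**3. Numbers per arm**

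The plan recruits 32, that is 16 per group, against a rule of thumb of 12 per group for continuous variables. With the plan's attrition figures:

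- at 20%: 16 × 0.80 = 12.8 per arm
- at 30% (6 months): 16 × 0.70 = 11.2, about 11 per arm

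The present point does not depend on how 32 was reached.

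**4. Precision of a prevalence difference (illustration only)**

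Assume the same prevalence p in both arms and n per arm. The normal-approximation 95% half-width is 1.96 × √(2p(1 − p)/n).

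- p = 0.20, n = 11: 1.96 × √(0.32/11) = 0.334, about 33 points
- p = 0.37, n = 11: 1.96 × √(0.4662/11) = 0.404, about 40 points
- p = 0.50, n = 11: 1.96 × √(0.50/11) = 0.418, about 42 points
- p = 0.37, n = 16 (no attrition): 1.96 × √(0.4662/16) = 0.335, about 33 points

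The Background gives 37% as an upper figure for all cardiac surgery patients. Entrants here are selected for pain, so their prevalence may differ; hence the range of 20% to 50%, which is an assumption.

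**5. Dilution (illustration only)**

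Suppose a share f of participants in each arm would be counted as cases at follow-up because of pain that predates surgery, whatever their allocation. The risk difference over all participants is then (1 − f) times the difference among the rest. The article gives no value for f. At an assumed 10% the multiplier is 0.90; at an assumed 30% it is 0.70. If the intervention also eases long-standing pain, the dilution is smaller.

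**The case against.** The case on the other side has real force, and several points stand.

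- **A reader might infer that the trial cannot report CPSP prevalence.** The document does not support that. Pain is rated at 3 and 6 months, the CPSP gloss has no severity cut-off, and the general line on categorical outcomes would accommodate a crude proportion. What is lacking is a named case variable.
- **A reader might infer that the plan contradicts its own definition of CPSP.** It does not. The exclusion of other causes belongs to persistent postoperative pain; the CPSP gloss in the same paragraph has no such clause.
- **A reader might infer that a rate for planning the next trial is biased.** The sample-size rationale speaks of means and variances for continuous variables. No prevalence is named as a planning input.
- **The interview wording is not shown.** The questionnaire may already ask about site or onset, so the point holds only for the items as described.
- **Bias between arms is limited.** Allocation is randomised and the models adjust for baseline values, which partly accounts for pain already present at entry. What remains is dilution, and chance imbalance in small arms.
- **The consequence is modest.** The Objectives list intensity, interference and opioid use, without prevalence, and the analyses are called illustrative.

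It can also be said that a cut-off is ordinary content for an analysis plan that is not shown. That is fair for the cut-off itself. It does not remove the mismatch, because the article lists its outcomes and explicitly equates prevalence and severity with three measures that are not case status.

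**Conclusion.** The concern holds as a mismatch between target and analysis. The effect on CPSP prevalence is placed in the primary interest, and the analyses as listed do not estimate it. As described, entry and measurement do not separate surgical-site pain from pre-existing pain, and the one variable that would help has no stated use, so long-standing pain may count as CPSP and dilute a preventive contrast.

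The conclusion rests on the text and not on the arithmetic. The arithmetic shows that a prevalence difference at 6 months would be very imprecise, about 33 to 42 points either side under the assumed 20% to 50% prevalence with 11 per arm, so it should be presented as descriptive. The extent of dilution cannot be determined from the document, because it does not give the share of participants with earlier chronic pain. The change is worth making but is not critical to an unpowered pilot.

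**What to change.** 1. **Define a CPSP case at T2 and T3 on an existing item.** For example, worst pain of at least 1 for any CPSP, and at least 4, the threshold the plan already uses at entry, for moderate to severe CPSP.
2. **Report it descriptively.** Give the proportion per arm and the risk difference with a score-based 95% CI, which suits about 11 per arm better than the normal approximation used above.
3. **Use the variable already collected.** Repeat the pain analyses without participants who had documented chronic pain before surgery, as a sensitivity analysis.
4. **If the questionnaire does not already ask it, add one question** at the remaining T2 and T3 visits: is the pain at or around the surgical site, and did it begin or worsen after surgery?

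If the sponsor does not want a case definition, the alternative is to remove prevalence from the statement of primary interest and keep severity, which the listed models do address.

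Steps 1 to 3 cost only wording and use data already planned. Step 4 adds one question; because recruitment has begun, participants already past a visit will lack the item there. The sensitivity analysis will be small and should be read as such.

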## Results

Recruitment began in June 2021. Although several clinical settings expressed a great interest for the study and type of intervention, recruitment is not progressing as expected as passive recruitment strategies were used because of the current pandemic. The decrease of elective procedures such as cardiac surgeries during surge of COVID-19 cases is also a considerable barrier. The recruitment process is constantly monitored by the research team, discussed with clinical partners, and updated according to the latest data and restrictions related to COVID-19. Data collection is expected to be completed by March 2022.

## Discussion

### Principal Implications

Pain after cardiac surgery is the most common symptom. However, multiple challenges still exist regarding its management [111]. The impact of unrelieved pain after cardiac surgery can be long lasting and can even influence the trajectory of cardiovascular disease [10,11]. For a few years now, a multimodal approach has been the gold standard for postoperative pain management [112]. Our previous work has demonstrated the potential to influence pain management behavior and postoperative recovery in the first days after surgery with a brief intervention if content targets specific psychosocial risk factors for CPSP. Most importantly, the intervention approach targets psychological factors that play an important role in the transition from acute to chronic postoperative pain. A logical next step in this research regarding the prevention of CPSP is to explore the potential impact of such interventions on pain after discharge from the hospital when patients are more isolated and need to self-manage their pain. In addition to our preliminary work in the acute phase, an intervention tackling pain in the different phases of the perioperative continuum could be proposed. The ultimate goal is to prevent the development of chronic pain and associated disability and opioid misuse.

### Significance of Intended Outcomes

Achieving these aims is significant because they directly target the trajectory of CPSP, a leading cause of disability and opioid misuse. This approach is innovative because it promotes pain self-management through the enhancement of individual protective factors and modulation of individual risk factors. Further MBI for pain is fairly recent and has not been examined for its potential role in preventing chronic pain. Of note, preventing the transition to chronic pain and reliance on opioids while promoting patient engagement and care accessibility is closely in line with the National Institute of Health’s National Pain Strategy [23] and Helping to End Addiction Long-term initiative [113]. Finally, the lack of continuity of care has emerged as a barrier to the prevention of CPSP [111]. With the proposed approach, patients can access the intervention at their convenience and according to their needs but also gain autonomy through a self-management approach. Indeed, the use of interactive technologies helps address the challenges of continuity of care between the different phases, as well as accessibility to health education and evidence-based quality pain care, which is a current national concern [23].

### Conclusions

This funded pilot RCT will examine the acceptability, feasibility, and preliminary efficacy of a web-based MBI for the prevention of CPSP during the recovery period after discharge from hospital. The results of this study will inform current clinical guidelines promoting a multimodal approach to pain management and continuity of care. If successful, the intervention could be expanded to numerous surgical populations at risk of developing CPSP, such as orthopedic surgical patients and other patients at risk for chronic pain, persons with work-related injuries, or persons living with a chronic disease. After further evaluation, a brief and cost-effective intervention could be introduced to hospitals, rehabilitation programs, and other primary care settings to support clinicians and patients in their partnership for the prevention of CPSP. The high potential of integration of the intervention in established care programs, such as rehabilitation programs, is promising for its uptake and sustainability.

## Appendix

Multimedia Appendix 1 Peer-reviewer report from Florida State University's Council on Research & Creativity.

## Abbreviations

ACG: attention control group
CPSP: chronic postsurgical pain
EG: experimental group
MBCT: mindfulness-based cognitive therapy
MBI: mindfulness-based intervention
PI: principal investigator
RA: research assistant
RCT: randomized controlled trial
